# Design and rationale of the REStoring mood after early life trauma with psychotherapy (RESET-psychotherapy) study: a multicenter randomized controlled trial on the efficacy of adjunctive trauma-focused therapy (TFT) versus treatment as usual (TAU) for adult patients with major depressive disorder (MDD) and childhood trauma

**DOI:** 10.1186/s12888-023-04518-0

**Published:** 2023-01-17

**Keywords:** Major Depressive Disorder, Childhood Trauma, Trauma-Focused Therapy, Imagery Rescripting, Eye Movement Desensitization and Reprocessing, Randomized Controlled Trial

## Abstract

**Background:**

Major depressive disorder (MDD) is a common, recurrent mental disorder and a leading cause of disability worldwide**.** A large part of adult MDD patients report a history of childhood trauma (CT). Patients with MDD and CT are assumed to represent a clinically and neurobiologically distinct MDD subtype with an earlier onset, unfavorable disease course, stress systems’ dysregulations and brain alterations. Currently, there is no evidence-based treatment strategy for MDD that specifically targets CT. Given the central role of trauma in MDD patients with CT, trauma-focused therapy (TFT), adjunctive to treatment as usual (TAU), may be efficacious to alleviate depressive symptoms in this patient population.

**Methods:**

The RESET-psychotherapy study is a 12-week, single-blind, randomized controlled trial testing the efficacy of TFT in 158 adults with moderate to severe MDD, as a ‘stand-alone’ depression diagnosis or superimposed on a persistent depressive disorder (PDD), and CT. TFT (6–10 sessions of Eye Movement Desensitization and Reprocessing and/or imagery rescripting) + TAU is compared to TAU only. Assessments, including a wide range of psychological/psychiatric and biological characteristics, take place before randomization (T0), during treatment (T1), at post-treatment (T2) and at 6-month follow-up (T3). Pre-post treatment stress-related biomarkers in hair (cortisol) and blood (epigenetics and inflammation) will be assessed to better understand working mechanisms of TFT. A subgroup of 60 participants will undergo structural and functional Magnetic Resonance Imaging (MRI) assessments to determine pre-post treatment brain activity. The primary outcome is self-reported depression symptom severity at post-treatment, measured with the 30-item Inventory of Depressive Symptomatology – Self Report (IDS-SR).

**Discussion:**

If adjunctive TFT efficaciously alleviates depressive symptoms in MDD patients with CT, this novel treatment strategy could pave the way for a more personalized and targeted MDD treatment.

**Trial registration:**

ClinicalTrials.gov, registered at 08–12-2021, number of identification: NCT05149352.

**Supplementary Information:**

The online version contains supplementary material available at 10.1186/s12888-023-04518-0.

## Background

Major depressive disorder (MDD) is a common, recurrent mental disorder and a leading cause of disability worldwide, related to poor health behaviors, increased mortality risk and high societal costs [1–3]. MDD is not a unitary disease entity but a heterogeneous disorder with high levels of comorbidity [4–6].

One of the most potent and robust risk factors for MDD is exposure to childhood trauma (CT), often defined as the experience of emotional/physical/sexual abuse and/or emotional/ physical neglect before the age of 18 [7–11]. Several meta-analyses have estimated the worldwide prevalence of CT to be high, with prevalence rates between 12 and 27% [12–15]. In adult MDD, CT prevalence is around 20—63% (depending on studies’ CT definition), with highest prevalence rates in persistent depressive disorder (PDD) and emotional neglect (43—58%) and emotional abuse (37—52%) as the most commonly reported CT types [7, 9, 16, 17]. MDD with CT is considered to be neurobiologically distinct from MDD without CT, with 1) dysregulations of the major stress systems (i.e. aberrant cortisol levels [18, 19] and elevated inflammation ( [20, 21]), 2) alterations in stress-susceptible brain regions, (i.e. amygdala hyperreactivity ( [22, 23]), medial prefrontal cortex (mPFC) hypoactivity) [24]), and 3) reduced brain connectivity in limbic, salience, and default-mode networks, which are involved in emotion regulation and self-reflective processing [23, 25]. Moreover, MDD in patients exposed to CT has been assumed to be a clinically distinct MDD subtype with an earlier onset, more severe, chronic and recurrent symptoms and high comorbidity [9, 26–29]. When it comes to depression treatment response in patients with CT, findings are inconsistent. Meta-analytic findings of studies published up to 2013 showed that MDD patients with CT have poorer treatment outcomes following (combined) treatment with psychotherapy and pharmacotherapy when compared to their non-CT counterparts [8, 28]. However, in a recent meta-analysis, these findings were not replicated as results showed that depressive adults with CT experienced significant and similar symptom improvement compared to those without CT [16]. Yet, patients with CT reported higher depression symptom severity at baseline and after treatment [16], consistent with former meta-analytic findings of CT being associated with lower remission rates after depression treatment [28]. In turn, the presence of residual depressive symptoms after treatment has been proven to be a predictor of depression relapse and recurrence [30]. Hence, depressive patients with CT are disadvantaged and less likely to meet the criteria for remission following first-line depression treatments, which advocates for the use of additional (trauma-focused) interventions to further alleviate depressive symptoms in this MDD subtype. Although research on personalized treatments for depression, targeting underlying transdiagnostic factors and mechanisms, is growing [31], there is currently not yet an evidence-based treatment strategy for MDD patients with CT that specifically targets CT. This is problematic as CT is highly prevalent in adult MDD and a pivotal risk factor for an unfavorable disease course [9, 27–29]. Therefore, there is a pressing need for novel treatment strategies that might alleviate depressive symptoms in MDD patients with a history of CT.

Given the central role of trauma in patients with MDD and CT, trauma-focused therapy (TFT) may be effective for this MDD subtype. Effective, evidence-based TFTs, such as trauma-focused cognitive behavioral therapy (TF-CBT), prolonged exposure (PE), imagery rescripting (ImRs) and Eye Movement Desensitization and Reprocessing (EMDR) are well investigated and first-choice treatments for posttraumatic stress disorder (PTSD) [32–36]. MDD and PTSD often co-occur, with a high prevalence (around 50%) of PTSD and comorbid MDD [37], and prevalence rates of around 9 – 36% for MDD and comorbid PTSD [38, 39]. The presence of CT has considered to be a relevant risk factor for affective disorders and comorbid PTSD [39]. Intrusions and (experiential) avoidance, main symptoms that define PTSD, also occur in patients with depressive disorders and might play an important role in maintaining depressive symptoms [40]. In fact, a recent meta-analysis showed that adults with MDD were as likely to experience intrusive memories as adults with PTSD [41]. Although TFTs that target PTSD symptomatology have been shown to reduce comorbid MDD symptoms in PTSD patients [34, 42–45], controlled studies on TFT’s efficacy for mental disorders other than PTSD are relatively scarce. A recent meta-analysis concluded that EMDR can be an effective treatment for patients with a depressive disorder and a history of adverse events, in the absence of PTSD [46]. However, included studies generally had a small sample size with inactive control conditions (e.g. waitlist) and EMDR was focused on aversive events in both childhood and adulthood. For ImRs, several studies have shown promising results regarding the efficacy of this treatment for MDD outside a PTSD diagnosis [47–49], although CT was not necessarily the focus of treatment. Thus, even though CT is highly prevalent in MDD patients, no specific, tailored evidence-based treatment strategy currently exists that specifically targets the detrimental effects of CT in this MDD subtype.

The overall aim and primary objective of the RESET-psychotherapy (REStoring mood after Early life Trauma) study is to investigate whether TFT as an adjunctive to treatment as usual (TAU) (experimental condition) leads to more reduction of depressive symptoms at post-treatment when compared to TAU only (control condition) in MDD patients with CT. Secondary objectives are: 1) to determine whether patients who receive adjunctive TFT show more depressive symptom reduction during treatment and at 6-month follow-up than patients who only receive TAU, 2) to examine whether patients in the experimental condition show more improvement in other clinical outcomes in comparison to patients in the control condition (i.e. MDD remission rate, anxiety symptom severity, insomnia, subjective stress and overall functioning and disability), 3) to examine potential mediators (e.g. social support and stressful life events) and moderators (e.g. comorbid PTSD / acute stress disorder (ASD), timing/duration/context of CT, resilience, personality and coping) of the hypothesized beneficial effect of TFT, and 4) to understand neurobiological mechanisms of the expected clinical improvement following TFT.

## Methods

### Study design

The RESET-psychotherapy study is a 12-week, multicenter, single-blind, superiority RCT with two treatment arms: 1) TAU and 2) TAU + TFT. In total, 158 adult MDD patients with CT are randomly allocated (1:1) to one of the two treatment conditions (see ‘Sample size’ for the power analysis). A subgroup of 60 participants (*n* = 30 in each treatment group) will be invited to participate in a neuroimaging (functional Magnetic Resonance Imaging (fMRI)) sub-study to assess pre-post treatment brain activity. The RESET-psychotherapy trial adheres to the SPIRIT guidelines and methodology [50] (see Additional file 1: Appendix A for the populated SPIRIT checklist).

### Recruitment and study settings

Participants are recruited in routine clinical settings of multiple sites of three mental health organizations in the Netherlands, namely GGZ inGeest, HSK and Altrecht (see Additional file 1: Appendix D for a list of study sites). More mental health organizations may be involved in the near future to optimize the recruitment process. Clinicians give information about the main study and fMRI sub-study and refer possibly eligible patients to the study website (www.jeugdtrauma-depressie.nl) to complete online screening questionnaires about CT (short form of the Childhood Trauma Questionnaire (CTQ-SF) [51]) and depressive symptoms (Inventory of Depressive Symptomatology – Self Report (IDS-SR) [52]). After completing the questionnaires, a research assistant (RA) contacts the patient by telephone to ask whether the patient has any additional questions about the study and to screen for exclusion criteria. Randomization takes place after the baseline assessment. All participants in the RESET-psychotherapy study will be asked to participate in the fMRI sub-study (expected start in September 2022). If the patient is eligible and willing to participate, the fMRI measurements will be conducted at the Spinoza center for neuroimaging in Amsterdam.

### Eligibility criteria

Inclusion criteria are: 1) age ≥ 18 years, 2) a primary diagnosis of MDD, as a ‘stand-alone’ depression diagnosis or superimposed on a PDD (i.e. the current major depressive episode (MDE) should constitute the reason and focus of treatment), confirmed with the Mini International Neuropsychiatric Interview—Simplified (MINI-S) [53] for the fifth edition of the Diagnostic and Statistical Manual of Mental Disorders (DSM-5) [54], 3) moderate to severe MDD, as reflected by a score of  ≥ 26 on the IDS-SR [52], 4) moderate to severe CT, operationalized as scoring above the validated cut-off scores on one of the domains of the CTQ-SF (physical neglect, score ≥ 10; emotional neglect, score ≥ 15; sexual abuse, score ≥ 8; physical abuse, score ≥ 10; emotional abuse, score ≥ 13) [51], and 5) an adequate mastery of the Dutch language.

The following exclusion criteria are checked during a telephone screening, based on self-report following explicit questions: 1) a primary diagnosis of PTSD or ASD (which is also assessed during the baseline assessment, using the PTSD and ASD section of the MINI-S), 2) a lifetime diagnosis of borderline personality disorder (BPD), 3) a comorbid diagnosis of a severe mental disorder, such as bipolar disorder or a psychotic disorder, 4) current substance use dependence, and 5) previously having received TFT, specifically aimed at CT. Additional exclusion criteria for the fMRI sub-study are major internal or neurological disorders, claustrophobia, being pregnant and known contra-indications for MRI investigations, such as the presence of metal objects (e.g. pacemaker, arteriovenous clips).

### Sample size

Based on earlier results of an add-on TFT on depressive symptoms [55, 56] we estimate to detect a medium-sized between-group effect size (i.e., Cohen’s *d* = 0.50) on the primary outcome measure (depression symptom severity at post-treatment). Based on this assumption, a power of 0.8 (80%) and a two-tailed significance level of p < 0.05, the recruitment of 63 participants per treatment group is required. Considering a conservative drop-out estimate of around 20%, *n* = 79 patients per treatment group are needed, resulting in a total sample size of *n* = 158. As described by Thirion et al. (2007), fMRI analyses require a minimum of 20 participants per group for sufficient reliability [57]. However, to increase power, we strive to recruit more participants for the fMRI sub-study, aiming at a total sample of *n* = 60 (30 participants per treatment group).

### Study procedures

#### Informed consent and baseline assessment

The RESET-psychotherapy study was approved by the Medical Research Ethical Committee (MREC) of the Amsterdam UMC location VUmc. Participants must personally sign and date the informed consent (IC) form before any study-specific procedures are performed. The IC procedure is executed by authorized RA’s. Written and verbal versions of the patient information letter and IC is presented to the participants, detailing the exact nature of the study, the implications and constraints of the protocol and any risks involved in taking part. After the participant has signed the IC, the two-hour baseline measurement is conducted by a RA (Fig. 1). During this assessment, a wide range of data is collected, see Table 1. The biological samples are only collected if the participant explicitly gives consent in the IC. Participants in the fMRI sub-study are asked to sign the IC of this sub-study during the first fMRI measurement before undergoing the fMRI scans (see ‘ Assessments, outcomes and instruments’ for the fMRI scanning protocol). The one-hour pre-treatment fMRI measurement must occur within 2 weeks after the baseline measurement (Fig. 1). If this is not possible, the patient cannot participate in the fMRI sub-study.

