#### Randomization and blinding

Upon completion of the baseline assessment, patients are randomized by the coordinating researcher of the participating center (Fig. 1). Permuted block randomization is used, stratified per participating site, using Castor EDC software. Patients are randomly assigned to the control condition (TAU) or the experimental condition (TAU + TFT) on a 1:1 basis. Due to the nature of the TFT, patients and therapists are aware of the allocated arm. However, outcome assessors are kept blind to the allocation, in accordance to the CONSORT guidelines [58]. Unblinding of the outcome assessors is not permissible and the outcome assessors are instructed to remind participants to not disclose the nature of their treatment.

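### fMRI sub-study consent and the first scan appear to follow allocation, although the scan is labelled T0, which the abstract places before randomization

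*Protocol article*

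**What the plan says.** The section Informed consent and baseline assessment describes two separate visits. The first is the main baseline visit: "After the participant has signed the IC, the two-hour baseline measurement is conducted by a RA". The second is the scan: "The one-hour pre-treatment fMRI measurement must occur within 2 weeks after the baseline measurement"; a patient who cannot meet that window is left out of the sub-study. Consent to the sub-study belongs to the second visit: "Participants in the fMRI sub-study are asked to sign the IC of this sub-study during the first fMRI measurement before undergoing the fMRI scans".

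Randomization is tied to the first visit. Randomization and blinding says "Upon completion of the baseline assessment, patients are randomized by the coordinating researcher of the participating center", and Recruitment and study settings agrees: "Randomization takes place after the baseline assessment". Patients and therapists know the arm; outcome assessors do not.

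The labels point the other way. The abstract says that assessments "take place before randomization (T0), during treatment (T1), at post-treatment (T2) and at 6-month follow-up (T3". The neuroimaging section and Table 1 both put the first scan at T0, although the table legend defines T0 only as baseline. The scan is also called pre-treatment.

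Three further points bear on the question. Clinicians mention the sub-study at referral, and every participant is to be asked (Recruitment and study settings). The target is 60 participants, 30 per arm (Sample size). The MRI mixed model has time indicators and treatment-by-time interactions as its independent variables (Statistical analysis plan).

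**The concern.** If patients already know their arm when they sign for the sub-study, willingness to be scanned can differ between arms. TFT patients also have extra appointments to fit in, and the two-week limit removes anyone who cannot be scheduled. The scanned groups would then no longer be protected by randomization in the way that the full trial arms are.

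A scan made after allocation may also reflect expectancy and, if TFT has begun, early treatment. The pre-post comparison by arm would start from a measurement that is not a clean baseline. What is at stake is the MRI part of the fourth secondary objective, on neurobiological mechanisms. Hair cortisol and the blood markers serve that objective as well.

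**Working it through.** **1. Order of events.** Setting the sections side by side:

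| Event | Timing in the text | Section |
|---|---|---|
| Baseline measurement | day 0 | Informed consent and baseline assessment |
| Randomization | on completion of the baseline assessment | Randomization and blinding; Recruitment and study settings |
| Sub-study consent | at the first scan visit | Informed consent and baseline assessment |
| First scan | up to 2 weeks after the baseline measurement | Informed consent and baseline assessment |
| T0, including the first scan | before randomization | Abstract, with the neuroimaging section and Table 1 |

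The first four rows agree with the last only if randomization waits for the scan, or if the scan counts as part of the baseline assessment for sub-study patients. No section says either. The natural reading is baseline, randomization, sub-study consent, scan.

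**2. Is pre-treatment assured?** The Table 1 footnote describes the IDS-SR at weeks 2, 4, 8 and 10 as taken during treatment. T1 and T2 are counted from baseline. If week 2 is counted the same way, the scan window closes at a point that the protocol itself regards as during treatment. TFT runs over 12 weeks and T2 is nominally 12 weeks after baseline, so the nominal schedule leaves no two-week wait, although the T2 window extends to 14 weeks. No start date for TFT is given.

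**3. Bounds on treatment before the scan.**
- Lower bound: 0, if TFT starts after the scan.
- Upper bound as a share of the period: 2/12 = 17% (2/14 = 14% to 2/10 = 20% across the T2 window).
- Upper bound in sessions, assuming that TFT starts at once and sessions are evenly spaced: 6 × 2/12 = 1.0 to 10 × 2/12 = 1.7.

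**4. Share of the trial affected.** The plan's total reproduces: 2 × (1.960 + 0.842)² / 0.50² = 62.8, so 63 per arm; 63/0.80 = 78.75, so 79; total 158. The sub-study is 60/158 = 38% of it.

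**5. Does the per-arm target need entry after allocation?** Suppose 60 entrants are fixed before allocation and fall at random among 79 + 79. The hypergeometric probability of at least 20 per arm (the minimum that the protocol cites) is 0.999, and of 25 to 35 per arm 0.93. Consent before randomization does not threaten the sub-study's size.

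**6. The model.** The listed terms include no treatment main effect. If the interactions leave out T0, the model forces equal arm means at T0, which measurement before randomization justifies and arm-dependent entry does not. If the interactions include T0, no equality is imposed. The article does not say which.

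**The case against.** The strongest reply is that the order is an inference. No sentence says that the scan follows randomization. The scan is called pre-treatment and labelled T0, and a sub-study patient's baseline assessment might be meant to include it. Both relevant sections cite Fig. 1 for the sequence. That figure could not be read here and should be checked first. This stands as a limit on certainty. It does not remove the conflict, because the text nowhere holds randomization for the scan.

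Arm-dependent entry is also a possibility and not an established fact. Patients hear of the sub-study at referral, all are asked, and signing at the scanner is not the same as first deciding there. That softens the selection risk without closing it.

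A reader might go further and infer that the pre-post effect is attenuated by 17%. That needs TFT to start on the day of baseline, every scan to fall on day 14, and the brain effect to grow linearly. The documents state none of these. A figure of about 10% for a model with equal baselines (0.6 × 0.167) also needs an assumed pre-post correlation of 0.6; correlations of 0.4 to 0.8 would give 7% to 13%. If TFT starts after the scan, both figures are zero.

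A reader might likewise call this an open trial. It is single-blind: patients and therapists know the arm, but outcome assessors do not.

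**Conclusion.** The point holds as a conflict in the protocol with a real but unquantified risk. As written, sub-study consent and the first scan can follow allocation, and most naturally do, while the T0 label says otherwise. If they do follow it, entry can depend on the known arm and the MRI baseline may carry expectancy and possibly early treatment. Neither effect can be sized from the documents. Treatment before the scan lies between zero and about 2 of 12 weeks, and there are no data on uptake by arm. It cannot be concluded that the MRI comparison is biased, nor that scans were made after TFT sessions. The effect is confined to the fMRI sub-study and one part of a secondary objective; the primary IDS-SR analysis is untouched.

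**What to change.** - **Consent.** Obtain fMRI sub-study consent at the existing baseline visit, before randomization. This adds no visit and removes most of the scope for arm-dependent entry.
- **Text.** Reconcile the abstract, Informed consent and baseline assessment, Randomization and blinding, and the neuroimaging section with Table 1 on whether the first scan precedes randomization. If it does not, do not describe it as made before randomization.
- **Scan timing.** Where the scan slot allows, scan before allocation is executed or disclosed. This has a cost: T2 is timed from baseline, so any wait shortens the interval from allocation to T2. A full two weeks would cut it from 12 to 10 weeks (17%) in up to 38% of participants, and this would reach the primary outcome. Any wait should therefore be short.
- **Records.** For every sub-study participant, including those already scanned, record the first scan's date relative to randomization and to the first TFT session. Report uptake by arm.
- **Analysis, if scans follow allocation.** Add one sensitivity MRI mixed model that does not assume equal arm means at T0, and one restricted to scans made before any TFT session. The first addresses imbalance from selection. It does not correct an early treatment effect, and under the illustrative assumptions above it would move towards the larger attenuation, so it should accompany the planned model and not replace it.
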